#### Diabetes treatment satisfaction

The DTSQs and the DTSQ-change (DTSQc) are validated self-report measures of a participant’s current treatment satisfaction, and consist of an 8-item adult version (18 + years of age) and 12-item teen version (13–17 years of age), and a 14-item parent version that measures a parent’s satisfaction with their teen’s (ages 13–15 years) diabetes treatment [38]. The DTSQs Parent/Teen are used at baseline and follow-up to provide a ‘difference’ score for comparison. Scores can be compared between teens and their parents’ reports. The DTSQc has been developed to overcome potential ceiling effects, where respondents score near-maximum satisfaction at baseline and would therefore show little or no improvement at follow-ups [38]. Participants will complete the DTSQs at baseline and both the DTSQs and DTSQc at 12-weeks, to assess changes baseline, end of study and change in diabetes treatment satisfaction.

#### Health status

The EQ-5D-5 L (adults) and EQ-5D-Y-L (youth, ages 4–16 years of age) questionnaires provide standardised measures of health status, to describe health across a wide range of diseases [39]. The instrument comprises five dimensions (mobility, self-care, usual activities, pain/discomfort and anxiety/depression), and within each dimension there are five response levels (no problems through to extreme problems). Participants will be asked to indicate their health state by checking the box next to the appropriate response level for each dimension. The adult questionnaire has been validated in NZ and is available in English and Te Reo Māori, both options will be available depending on participant preference [40]. For the youth questionnaire, the validated version is available in English (UK) only. Participants will complete the questionnaire at baseline, and again at 12-weeks to assess the change in health status after starting on AID.

#### Nutrition education effectiveness

To assess the effect of nutrition education, of those who were invited to attend an education session (i.e., those participants with lower baseline carbohydrate counting skills), glycaemic metrics at 12-weeks will be compared for those who did, and did not attend. Participants will also be asked about their experience engaging with the study Dietitian during the qualitative interview which will provide lived experienced and contextual feedback specifically about the nutrition education provided.

#### Qualitative interviews

In brief, audio recordings from the semi-structured interviews with both participants and clinical staff will be transcribed verbatim, and recordings will be deleted thereafter. Nvivo software will be used to conduct a thematic analysis to identify Hub satisfaction and acceptability (for interviews with study participants), and factors that supported and hindered clinician self-efficacy in managing AID (for interviews with clinical staff). Themes will be compared between members of the analysis team until consensus is reached. For study participants, age, sex, insulin regimen, and duration since diagnosis will be taken from clinical records in order to describe the sample. For clinical staff, age, sex, and occupation/role will be collected in order to describe the sample. The qualitative sub-study of the experience of Māori participants in the ACCESS-AID study will be guided by the principles of decolonising methodologies [41] challenging western research practices to centre the needs, voices, and expectations of Māori participants and whānau. Interviews with Pacific participants will be managed in culturally appropriate ways with consideration to relevant Pacific health models.

#### Self efficacy questionnaire

Self-efficacy refers to an individual’s belief in their capacity to execute behaviours necessary to produce specific performance attainments [42]. In this context we would like to assess clinical staff’s self-efficacy related to managing patients with T1D who are using AID. A questionnaire has been developed specifically for this study and independently reviewed. This will be used to assess aspects of self-efficacy specifically related to AID management. This will be completed prior to the first day of employment with the Hub, and during staff members final week employed by the Hub, to assess changes in self-efficacy.

#### Existing workforce capacity building

A weekly or fortnightly drop-in webinar series is proposed to support healthcare professionals across Aotearoa in building confidence and capability in insulin pump and AID systems. Open to all clinicians with an interest in CGM and AID specifically those who have referred patients to the Hub, the series will explore a wide range of topics related to AID over time. Each one-hour session will include approximately 20 min of focused teaching on a specific aspect of pump therapy (e.g. interpreting pump data, managing exercise, conducting effective initiation appointments), followed by case-based discussion and Q&A. Case studies may be submitted in advance or brought to the session for collaborative discussion and clinical problem-solving, drawing on the expertise of the Hub’s clinical staff facilitators and peers. If no external cases are submitted, clinical staff will present relevant examples to support learning. A PowerPoint template will be provided to ensure consistent, anonymised case presentation, whether delivered by the contributing clinician or presented on their behalf. Educational content will be aligned with the forthcoming update to the Diabetes Nursing Knowledge and Skills Framework (and any other frameworks as suggested).

#### Cost-effectiveness analysis

To estimate the cost-effectiveness of the Hub, we will begin by establishing a control group comprised of individuals who initiate AID in NZ through their routine care providers. This control group will be carefully selected to match the intervention group (participants receiving care through the Hub). We will complete a cost-effectiveness analysis (cost per quality-adjusted life-years) in the intervention group compared to the control group. Markov model will be used for the cost-effectiveness analysis. The model construction and data analysis will be performed using TreeAge Pro. This study will be from the perspective of the health service in NZ, and only direct medical costs will be considered. The simulation process within the model will commence at the age of 18 years and will extend to age 100, providing a comprehensive view of the long-term impact of the Hub versus standard care.

#### Safety

SAEs will be managed as outlined in Sect. 2.6.3. All SAEs will be reported to the principal investigators of the study within one day of occurrence. Participants will also be advised to notify study staff of any adverse events related to the devices. This information will be used for internal safety monitoring. Technical support will be available to participants 24 h a day, and will be provided by device specific technical support services, as per usual care. Any device deficiencies (e.g., inaccurate labelling, device malfunction), will be recorded and reported to the device manufacturers as per usual practice.

### Statistical analysis

Pharmac, NZs pharmaceutical funding agency, estimates there are 18,000 to 21,000 people with pancreatic insufficiency (mostly T1D) living in NZ who would be eligible for funded CGM [11], of whom 85–90% were not using AID in 2023. We believe the Hub will facilitate approximately 500 new AID starts per year (provided by 2.4 full time equivalent clinical staff, per year).

A sample size of 500 or more participants will provide > 90% power, with a two-sided alpha of 0.05, to detect small changes in continuous outcomes (effect sizes ≥ 0.15) and estimate binary outcomes to within +/- 5%.

Numbers of people referred to the Hub, enrolled, and started on AID will be tabulated by the key demographic and clinical variables required for calculation of the prioritisation score as listed under Sect. 2.5.1.

Incidence proportions, stratified by region and priority subpopulations, will be calculated as the number of AID starts divided by the number of eligible people not on AID as estimated from national administrative datasets. For comparisons with other providers, an individual will be considered to have started on AID on the date they are first dispensed a subsidised pump as recorded by Health New Zealand.

Interrupted time series analysis will be used to investigate the impact that the Hub has on the rate of new AID starts nationally, and by region, Absolute numbers and incidence proportions of new AID starts will be calculated for consecutive time periods and displayed graphically. Generalised linear (Poisson) regression models will be used to estimate changes in the in the numbers and incidence of new AID starts before versus after deployment of the Hub. Differences between regions, such as workforce capacity, may be explored in models to identify facilitators and barriers to AID uptake.

Intervention effectiveness will be confirmed by descriptively summarising changes in Hub participants’ HbA1c and CGM metrics before versus after starting on AID.

National laboratory and CGM data is not available for those not enrolled in the study.

Incidence rates of adverse events will be calculated for study participants after AID start and compared to control populations utilising generalised linear regression models, adjusting for demographic factors (age, gender, ethnicity, NZ deprivation index). Controls will included study participants prior to AID start and non-study people with type one diabetes who have and have not started on AID.

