## Background

Automated insulin delivery (AID) systems are globally recognised as the gold standard for managing glucose levels in people with type 1 diabetes (T1D) [1, 2]. These systems link an insulin pump, continuous glucose monitor (CGM) and computer algorithm to semi-automate insulin delivery. AID systems have been shown to greatly improve glycaemic outcomes [3]. For example, in a randomised controlled trial of children and youth aged 7 to 25 years with above-target glycemia, HbA1c decreased by 2.5% (95% CI −3.1 to 1.8 [−27mmol/mol, 95% CI −34 to −20] *p* < 0.001) and time in range (TIR) increased by 35% (95% CI 28 to 41%) after using AID for 13-weeks, compared to the control group (multiple daily injections or continuous subcutaneous insulin infusion) [4].

Despite this evidence, in Aotearoa New Zealand (herein referred to as NZ) and worldwide, access to these advanced diabetes technologies is slow and inequitable [5–7]. Until recently in NZ, the main barriers to access included the lack of publicly funded CGM and restrictive eligibility criteria for insulin pump funding and consumables particularly for adults, people from low socioeconomic backgrounds, or ethnic minorities [5] with similar trends observed worldwide [8]. However, in October 2024, funding in New Zealand was expanded to include CGM and pumps for all people with type 1 and related forms of diabetes, enabling broader use of AID systems. Despite advances in technology and liberalisation of funding, many barriers to access remain. Historical treatment guidelines prioritised those who had more in-target glycemia and diabetes management skills [9, 10], effectively gatekeeping this technology from individuals who experience the greatest absolute benefits. Furthermore, workforce constraints, and sometimes overly complicated training and support pathways remain key barriers [11, 12] with evidence from the UK highlighting funded practitioner time as a key barrier for supporting individuals to use this technology [13]. Now more than ever, there is an urgent need to provide efficient and equitable access to AID for the thousands of individuals estimated to seek this technology in the coming years.

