#### Preparation for commencement of AID

After selection of their preferred AID system, participants will be provided with a prescription for all equipment required prior to the pump-start training. Special Authority and prescriptions will be completed by clinical staff who have a prescribing authorisation. Prior to commencement of AID, the Hub clinical staff will determine the initial pump settings based on at least two weeks of CGM data, their recent insulin dose history, as well as physical and biochemical measurements collected at baseline. Pump start settings will be sent to the Pump Trainer at least one week prior to training.

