### Outcomes

The primary outcome of this study is to assess the implementation effectiveness of the Hub. Secondary outcomes of this study include intervention effectiveness, safety and acceptability, psychosocial measures, nutrition education effectiveness, cost-effectiveness and clinical staff self-efficacy and intervention acceptability.

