#### Implementation effectiveness

Implementation effectiveness of the Hub, at facilitating AID starts and addressing inequities in care, will be assessed by determining the number and characteristics of people who are referred and enrolled by the Hub, and the time to discharge on AID. Counts of AID starts will be compared by provider (Hub versus all others) and over time (weekly from 12 months prior to Hub implementation until study end). Incidence proportions of new AID starts, and prevalence for overall AID usage, will be estimated nationally and by region for priority populations; Māori, Pacific, those living in rural areas, and those living in areas of highest socioeconomic deprivation as measured by the NZ deprivation index [37].

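### In the provider comparison, dating an AID start by the first subsidised pump misses earlier pump holders who move to AID and counts pumps that are not AID

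*Protocol article*

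**What the plan says.** The Outcomes section states that "The primary outcome of this study is to assess the implementation effectiveness of the Hub". Under Implementation effectiveness this includes a count comparison: "Counts of AID starts will be compared by provider (Hub versus all others) and over time (weekly from 12 months prior to Hub implementation until" the study ends). The same section adds incidence of new starts for Māori, Pacific, rural and most-deprived populations.

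The Statistical analysis section supplies the event definition. It opens with a limiting clause, "For comparisons with other providers, an individual will be considered to have started on AID", and fixes the date by rule: "an individual will be considered to have started on AID on the date they are first dispensed a subsidised pump", as recorded in Health New Zealand data. No other rule is given for identifying a start outside the Hub. The section then plans an interrupted time series with Poisson models for the national and regional rates of new starts.

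Three other places bear on the rule:

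- Background describes AID thus: "These systems link an insulin pump, continuous glucose monitor (CGM) and computer algorithm to semi-automate insulin delivery".
- Background names the main access barriers until recently as "the lack of publicly funded CGM and restrictive eligibility criteria for insulin pump funding and consumables", the latter particularly for adults, people from low socioeconomic backgrounds and ethnic minorities. Funding widened in October 2024.
- Study population does not exclude people who already use a pump, and under Preparation for commencement of AID, "participants will be provided with a prescription for all equipment required prior to the pump-start training".

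**The concern.** The protocol describes AID as three linked components but recognises a start by one of them, and only on its first subsidised dispensing. Two errors follow from a literal reading.

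- **Missed starts.** Pumps were subsidised for some people before funding widened. Someone who holds such a pump and changes to an AID system receives a pump that is not their first. The rule dates them to the old pump, so the real AID start is not a new start in the series.
- **False starts.** A first subsidised pump counts even if it is not AID-compatible or is used without CGM.

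These errors need not fall evenly. If earlier funding was hardest to obtain for ethnic minorities and people from low socioeconomic backgrounds, earlier pump holders should be more common outside those groups, and so should missed starts. That would distort the equity contrast that the primary outcome is meant to inform. It would also distort the Hub-versus-others contrast, because the Hub selects by a prioritisation score that favours some of the same groups.

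**Working it through.** **The plan's own figure.** The only stated power figure is for 500 participants, a standardised change of 0.15 and two-sided alpha of 0.05. For a single-arm change, power = Φ(0.15 × √500 − 1.96) = 91.8%, which agrees with the stated figure of over 90%. It concerns participants' own outcomes and is not affected by this point. The protocol gives no corresponding figure for the AID-start series.

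**Inputs from the protocol.** About 500 Hub starts per year (Statistical analysis). It gives no number of existing subsidised-pump holders, no share of pumps dispensed without CGM and no Hub start date.

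**Assumed inputs.**

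- u = share of true AID starts made by people who already had a subsidised pump (missed).
- v = share of recorded first pumps not used as AID (falsely counted).

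**Step 1: recorded against true starts.** Let T be true starts and R recorded starts. Starts that are both true and recorded can be written as T(1 − u) or as R(1 − v), so R/T = (1 − u)/(1 − v). With u from 0 to 0.4 and v from 0 to 0.5, R/T runs from 0.6/1 = 0.60 to 1/0.5 = 2.00. The two errors act in opposite directions, so the net sign is not known.

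**Step 2: Hub starts in the comparative series.** With u = 0.10 to 0.30 and v = 0:

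- Lost per year: 500 × 0.10 = 50 to 500 × 0.30 = 150, leaving 450 to 350.
- Per week: 500/52.18 = 9.6 true starts, recorded as 9.6 × 0.90 = 8.6 down to 9.6 × 0.70 = 6.7.

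**Step 3: before/after ratio when the true rate is flat.** The false ratio is R/T after divided by R/T before.

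| Before (u, v) | After (u, v) | R/T before | R/T after | False rate ratio |
|---|---|---|---|---|
| 0.20, 0.20 | 0.20, 0.20 | 1.00 | 1.00 | 1.00 |
| 0.10, 0.30 | 0.10, 0.05 | 1.286 | 0.947 | 0.74 |
| 0.10, 0.30 | 0.30, 0.05 | 1.286 | 0.737 | 0.57 |
| 0.30, 0.05 | 0.10, 0.05 | 0.737 | 0.947 | 1.29 |

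Constant misclassification cancels. Changing misclassification does not, and it can push the ratio either way.

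**Step 4: contrast between groups or providers.** With equal v, a ratio of counts for group A to group B is multiplied by (1 − u_A)/(1 − u_B). If u is 0.10 in A and 0.30 in B, the factor is 0.90/0.70 = 1.29; reversed, it is 0.70/0.90 = 0.78; if equal, it is 1.00. No shift over time is needed for this distortion.

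**The case against.** Four arguments on the other side have weight.

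1. **Scope.** The rule is introduced for comparisons with other providers. Numbers referred and enrolled, time to discharge, and the Hub's own tabulation of starts are not expressly tied to it, and the Hub has its own Day 0. This stands: a reader might infer that the rule governs the whole primary outcome, but the text does not say so. An effect on the incidence denominator is likewise only an inference, since that denominator is said to be estimated from national administrative data.

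2. **Condensed article.** A look-back period and code lists are details that an article commonly leaves to the full protocol. First could also mean first within the observation window, because the text does not say first ever. This stands in part. The point is not that detail is absent, however, but that the stated rule contradicts the article's own description of AID. The two readings of first also give different counts.

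3. **October 2024.** A reader might infer that the error changes at the funding date and therefore biases the before/after estimate. The documents do not establish this. The series begins 12 months before Hub implementation, whose date is not given. If the Hub began by about October 2025 the series reaches back to October 2024; if later, it does not. Nor was an earlier pump necessarily a pump without AID: the protocol puts 10-15% of 18,000-21,000 people, about 1,800-3,150, on AID in 2023. The two systems offered by the Hub are both AID systems, so the proxy may work reasonably well for recent first pumps.

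4. **A CGM condition in the main definition.** Requiring dispensed CGM throughout would push recorded starts towards zero before October 2024 and create an artificial step if that date is inside the series. This stands and shapes the fix.

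**Conclusion.** The point holds within limits. For provider comparisons, and by implication the national time series, the stated event is not an AID start as the protocol describes AID. Read literally, it omits earlier subsidised-pump holders who move to AID and admits pumps that are not AID.

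The size cannot be derived from the document. A loss of 50-150 of 500 Hub starts per year rests on the assumed 10-30% share, on reading first as first ever, and on applying the rule to Hub starts in the comparative series. The Hub's own count would be unaffected. The before/after ratio is biased only if misclassification shifts within the series; the false ratios of 0.57 to 1.29 illustrate assumed shifts and are not estimates.

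The distortion of provider and equity contrasts depends on the share of earlier pump holders differing between groups. Background makes that plausible for ethnicity and socioeconomic position. It is less clear elsewhere: Background also lists adults among those restricted, whereas the score favours people under 25, and it does not name rural residents in that sentence. The documents therefore support a risk of differential error, but not a direction for every subgroup.

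**What to change.** - **Main definition.** Define the start as the first dispensing of an AID-compatible pump, identified by product code, regardless of any earlier non-AID pump. Apply it identically to Hub and non-Hub starts.
- **Validation.** Compare the rule with the Hub's recorded Day 0 dates, report its sensitivity and lag, and carry both into a sensitivity analysis.
- **CGM.** Where national CGM dispensing data are available, add a sensitivity analysis that uses the later of pump and CGM dispensing, restricted to weeks after October 2024 so that it creates no artificial step. The Statistical analysis section says national CGM data are unavailable for people outside the study. This appears to mean glucose readings rather than dispensing, and should be clarified.
- **Funding date.** State the Hub start date. If October 2024 lies inside the series, handle it as a separate interruption.

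The cost is one reworded definition, a product code list and a small amount of extra coding. Some people remain imperfectly classified, which should be stated: those who already hold an AID-compatible pump and later add CGM, and those who fund their own CGM.

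### Addressing inequities is part of the primary outcome, but the only before/after model is scoped nationally and by region, so a change in the priority/non-priority access gap is not formally estimated

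*Protocol article*

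**What the plan says.** Under Outcomes, "The primary outcome of this study is to assess the implementation effectiveness of the Hub". Under Implementation effectiveness, the Hub's success "at facilitating AID starts and addressing inequities in care, will be assessed by determining the number and characteristics of people who are referred and enrolled", together with time to discharge. Two further elements follow:

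- **Counts.** "Counts of AID starts will be compared by provider (Hub versus all others) and over time", weekly from 12 months before the Hub.
- **Incidence and prevalence.** Incidence proportions of new starts and prevalence of AID use "will be estimated nationally and by region for priority populations": Māori, Pacific, rural, and the most deprived areas by the NZ deprivation index (NZDep).

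Under Statistical analysis, three statements bear on the point:

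- "Incidence proportions, stratified by region and priority subpopulations, will be calculated as the number of AID starts divided by the number of eligible people" not yet on AID, from national administrative data.
- The interrupted time series investigates "the impact that the Hub has on the rate of new AID starts nationally, and by region". Poisson models compare numbers and incidence before and after the Hub. The only effect modifiers mentioned are differences between regions.
- People referred, enrolled and started are "tabulated by the key demographic and clinical variables required for calculation of the prioritisation score".

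The Prioritisation score section gives 2 points for Māori or Pacific ethnicity and 1 for rural residence. Deprivation is not a score item. Invitation depends on the score and on study capacity.

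**The concern.** A claim that an access gap narrowed needs two groups compared over two periods. The time series supplies the two periods but, as scoped, no priority grouping. The stratified incidence supplies the groups, but no gap measure, no change in it and no interval is stated.

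This matters because of timing. The Background reports that funding was extended in October 2024 to everyone with type 1 and related diabetes, and the Discussion describes a period of peak uptake. Starts can therefore be expected to rise in all groups. A rise in priority-group incidence could be read as an equity success while the gap stayed the same or widened.

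The make-up of the enrolled group does not settle the matter, because on ethnicity and rurality it is largely a product of the score used to invite people. The flow table also follows the score's variables, so deprivation, a named priority population, is not among the variables listed for it.

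**Working it through.** **1. The plan's own figures.** For a within-participant change of 0.15 SD with n = 500, power = Φ(0.15 × √500 − 1.96) = 91.8%. The half-width for a binary outcome is 1.96 × √(0.25/500) = 4.4 points. Both agree with the stated figures (over 90%; within 5 points). They concern Hub participants and do not size an access comparison.

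**2. Scale of the Hub.** From Statistical analysis, 18,000 to 21,000 people are eligible and 85–90% were not on AID. The pool is 18,000 × 0.85 = 15,300 to 21,000 × 0.90 = 18,900. The expected 500 Hub starts a year are 500/18,900 = 2.6% to 500/15,300 = 3.3% of it.

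**3. Illustration.** From the documents: 500 Hub starts, and a pool of 17,000, which lies within the range above. Assumed, not in the documents: 25% of the pool is priority (4,250 against 12,750); 3,000 starts a year before the Hub, 15% of them priority (450 against 2,550); a fixed pool; no secular trend; one year before and one after.

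Before the Hub: 450/4,250 = 10.6%; 2,550/12,750 = 20.0%; ratio 0.53.

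After, with the national rate ratio 3,500/3,000 = 1.17 in every row:

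| Hub starts to priority groups | Priority incidence | Other incidence | Ratio | Change in ratio (95% interval) |
|---|---|---|---|---|
| 0% | 450/4,250 = 10.6% | 3,050/12,750 = 23.9% | 0.44 | 0.84 (0.73 to 0.96) |
| 5% | 475/4,250 = 11.2% | 3,025/12,750 = 23.7% | 0.47 | 0.89 (0.77 to 1.02) |
| 15% | 525/4,250 = 12.4% | 2,975/12,750 = 23.3% | 0.53 | 1.00 (0.87 to 1.15) |
| 60% | 750/4,250 = 17.6% | 2,750/12,750 = 21.6% | 0.82 | 1.55 (1.36 to 1.76) |

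The last column is the ratio after divided by the ratio before. Its log has standard error √(1/450 + 1/2,550 + 1/a + 1/b), where a and b are the priority and other starts after the Hub, assuming Poisson variance without overdispersion. For 60%: √(1/450 + 1/2,550 + 1/750 + 1/2,750) = 0.066.

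In the 5% and 15% rows priority incidence rises, yet the ratio falls or does not move. In the 15% row the absolute gap grows from 20.0 − 10.6 = 9.4 to 23.3 − 12.4 = 11.0 points (rounded from 10.98).

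**4. Sensitivity.** A second set of assumptions used a pool of 15,300, a pre-Hub ratio of 0.60, a priority share of 10–30% and 1,000–4,000 prior starts. With a 20% share and 2,000 prior starts, the national ratio is 1.25 throughout:

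| Hub starts to priority groups | Ratio after (0.60 before) | Approximate power of a group-by-period term |
|---|---|---|
| 5% | 0.52 | 37% |
| 20% | 0.67 | 27% |
| 40% | 0.90 | over 99% |
| 60% | 1.16 | over 99% |

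Across the whole grid, power is at least 68% when 40% of Hub starts go to the priority group. It can be below 10% when the Hub's mix is close to the existing one, because there is then little change to detect.

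**The case against.** A reader might infer that the plan cannot show whether the gap narrowed. The documents do not support that. Incidence and prevalence by priority population come from national data, not only from Hub enrollees. On the illustration's own numbers, planned priority incidence (10.6%, 11.2%, 12.4% or 17.6%) and planned national incidence (3,500/17,000 = 20.6%) together recover the complement by subtraction. Incidence is also to be plotted over consecutive periods. The scenarios are therefore separable descriptively, provided those series are split by priority group. The text does not say that they will be, but does not exclude it.

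A reader might also infer that the score fixes who enrols. It does not. Capacity and referral matter, several score items are clinical or occupational, and the referred are tabulated as well as the enrolled. Nor does the article say that the flow table is confined to score variables.

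Finally, interaction terms are often left to a full protocol or analysis plan, and neither is shown. This has weight against asking for more detail as such. It has less weight here, because the article does state the model's scope, and that scope omits its own primary equity question. The same section adjusts the adverse-event models for ethnicity and NZDep, so these variables are named for a secondary outcome but not in the access model for the primary one.

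**Conclusion.** The point holds in a limited form. The plan describes access by priority population but does not formally estimate a change in the priority/non-priority gap, although reducing inequity is part of the primary outcome. A rise in priority-group incidence alone would not show narrowing while funding is lifting uptake, and the enrolled mix is largely, though not wholly, a result of the score.

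The structural point rests on the text alone. Its possible size rests on assumed inputs: one national rate ratio of 1.17 is compatible with a gap ratio moving from 0.53 to anywhere between 0.44 and 0.82. The sponsor should make the change, but the planned data are not unfit for the question.

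**What to change.** In the Poisson time-series model, add priority-group-by-period terms (level and slope) for Māori, Pacific, rural and highest-NZDep people, each against its complement. Name the change in the priority/non-priority incidence ratio, with a 95% interval, as the equity estimate. Show the consecutive-period incidence for each group and its complement. Add NZDep to the referred–enrolled–started table; it should be derivable from the home address already used for rurality.

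The cost is some extra model terms and one table row. Ethnicity, deprivation, rurality and dispensing data are already needed for the planned stratified incidence. The price is statistical: wide intervals for small groups, wider still under overdispersion or when weekly series are split by region, and low power if the Hub's mix is close to the existing mix. An interval spanning no change should then be reported as inconclusive.
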